## Anticipated results

The expected outcomes of this study are divided by objective. First, in terms of rSO_2_ and cerebral oxygen metabolism, when examining the primary outcome of an absolute change in the percent change in rSO_2_ from baseline to the completion of surgery between intervention and control groups, significant fluctuations in rSO_2_ may not be observed in the control group throughout the surgery, but under the dual stress conditions of general anesthesia and surgical trauma, reasonable speculation is that older patients with fragile brain function most likely have a trend of a decrease during surgery, which may be attributed to the poorer cerebral vascular self-regulation and lower functional reserve in this subject population, therefore, that the absolute difference between their postoperative rSO_2_ values and their preoperative baseline values may be < 0. However, in the intervention group, PHC mediated by small tidal volume ventilation may exert a comprehensive cerebral protective effect through potential mechanisms such as cerebral vasodilation, improvement of cerebral microcirculation, maintenance of the balance of cerebral oxygen supply and demand, mitigation of free radical-induced damage, and inhibition of the inflammatory response and apoptosis. These changes may result in an increasing trend in the intraoperative changes in rSO_2_ in the intervention group. The absolute change of rSO_2_ values in the control and intervention group are significantly different, which is supported by evidence in a previous related study [71]. As mentioned previously, these possible mechanisms have been clarified in animal studies and clinical trials in recent years, and the selection of older patients with NFBF as subjects in the present trial to investigate the association between PHC and rSO_2_ is a reasonable approach and extension based on the existing research evidence.

In addition, we will also perform statistical analyses (calculated using Fick's formula) of the relevant indicators of cerebral oxygen metabolism, "DajvO_2_ and CERO_2_" because the exploration of the potential correlation mechanism *"PHC → improves cerebral oxygenation → improves postoperative cognition"* is another critical objective of this study, and the significant correlation between cerebral oxygen metabolism and postoperative cognitive dysfunction has been confirmed [72, 73]. Although few previous studies related to PHC and cerebral oxygen metabolism have been conducted, studies on the relationship between the two have produced contradictory results, with evidence of positive, negative, and no correlations having been reported [12, 74–76]. However, we maintain that the final findings will support the hypothesis that PHC accompanied by a higher rSO_2_ improves cerebral oxygen metabolism and reduces the incidence of DNR, thus improving cognitive function outcomes. In addition, our analysis of serum NSE and IL-6 levels by collecting blood samples may reveal significant differences between the two groups. The intervention group may be able to mitigate perioperative brain injury through the multifaceted brain-protective mechanism of PHC, and NSE and IL-6 levels will be lower than those in the control group as predictors of brain injury.

According to the logical stratification of this study, we included postoperative cognitive outcome as a secondary outcome, and graded these parameters quantitatively based on MMSE scale scores to assess the postoperative cognitive function status of the two groups and combined with the differences in the effects of PHC interventions on "rSO_2_, DajvO_2_, CERO_2_, NSE, and IL-6 levels" in the two groups, a multifaceted and multilevel approach will be used to verify the proposed mechanism of *"PHC → improves cerebral oxygenation → improves postoperative cognition."*

Other secondary findings, including surgical prognosis, postoperative complications, the incidence of adverse effects, and length of hospital stay, lack relevant clinical evidence and theoretical support and require us to explore the intrinsic associations through the specific trial process.

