In summary, when the three key factors of "older patients," "fragile brain function," and "CO_2_ pneumoperitoneum and laparoscopic surgery" are linked together, the protection of the perioperative cognitive function of patients must receive increasing attention. Notably, the change and adjustment of CO_2_ pneumoperitoneum pressure are extremely limited due to the essential requirement of a clear operative field for delicate surgical operations. However, it seems to be a pioneering prospect from the perspective of hypercapnia. First, although permissive hypercapnia was the intervention used in our study, in combination with clinical practice, mild hypercapnia itself is difficult to avoid in major laparoscopic surgery, and extreme ventilation parameter settings (high respiratory rate/high tidal volume) are often required to force normal conditions, which may exert adverse effects. Therefore, our intervention is different from that used in most other RCTs. We evaluated the advantages and disadvantages of both in terms of justifying their existence and acceptability in terms of medical factors, combined with the adverse effects (lung tissue traction injury, airway pressure damage, hyperventilation, respiratory muscle fatigue, tachycardia, etc.) of the forced manual setting of ventilation parameters to achieve a normal blood pH. Previous preclinical and clinical studies of the effects of hypercapnia on the central nervous system and postoperative cognitive function have largely produced negative results; however, further explorations are needed to determine whether this problem can be further improved when hypercapnia is converted to a more precise state of permissive hypercapnia.

Therefore, we will conduct a prospective, single-blind RCT. Laparoscopic colorectal surgery is used as the surgical method and older patients with NFBF are defined according to the "*Guidelines for the management of perioperative anesthesia in older patients in China*" [46], which are the main inclusion criteria used to explore our established hypothesis that the PHC group (H) will exhibit improved brain oxygenation and increased rSO_2_ compared with the target normal group (N) (Table 1). In addition, as a secondary objective, we will evaluate whether PHC affects postoperative cognitive outcomes and further verify the existence of the potential mechanism of "*PHC → improves cerebral oxygenation → improves postoperative cognition*."

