### Sample size calculations

According to data previously reported by our institution, rSO_2_ values at wakefulness range from 60 to 80% for elderly patients with NFBF, consistent with previous studies [69]. Although the earlier studies of cerebral oxygen monitoring did not address the point of "NFBF," we obtained the same rSO_2_ interval in the preoperative awake state, which does not mean that this discussion is meaningless. However, the natural state of elderly patients with NFBF may not be significantly different from the average population due to the body's compensation, but when entering the general anesthesia and surgery state, the lack of cerebrovascular self-regulatory reserve capacity and the regional cerebral microcirculatory disorders of these patients only become apparent with the intensification of the systemic stress response and the increase of hemodynamic fluctuations.

Interestingly, a "15%" change in rSO_2_ values at the end of surgery relative to baseline values in both groups is considered clinically significant [70]. However, we need to state that "15%" is a research inference made for the anti-Trendelenburg position, and the laparoscopic colorectal surgery in this study was the Trendelenburg position. Due to the apparent position difference, we cannot ignore the secondary changes in cerebral perfusion and CBF. Continuing to choose the "15%" cutoff may overestimate the effect on the intervention group. Therefore, we used the more conservative "10%" relative change as the clinically significant margin in our trial. A baseline rSO_2_ of 60% to 80% was used, and the absolute change in rSO_2_ from baseline to the end of surgery was assumed to be 0% in the control group according to the pilot study and 8% in the intervention group (a 10% increase from baseline rSO_2_ of 80%). The sample-size calculation for the test of difference was performed with the use of PASS 15.0.5 software, and the total sample size needed for an unpaired t-test was calculated to be 68 at a two-sided significance level of 5% and 90% power. Considering the loss of a follow-up rate of 10%, our final sample size will be 76 (evenly distributed between the two groups).

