**Fig. 3 Fig3:**
[figure not shown]
Flowchart of the algorithm for the eight-step cerebral oxygen intervention

The assessment of postoperative cognitive function, another important finding of this study, has important clinical implications for investigating the potential mechanism of " *PHC → improves cerebral oxygenation → improves postoperative cognition. "* In this trial, the occurrence of DNR is quantified by scoring using the MMSE scale. However, we need to be clear that if, in the final statistical analysis, we find that the cognitive status between the two groups is not statistically different, or if there is a statistical difference, there is a cognitive-related confounding factor such as ASA grade or age. This outcome is possible and acceptable because this trial is not originally designed to explore the quantitative relationship between hypercapnia and postoperative cognitive performance. Although previous clinical evidence for the association between intraoperative rSO_2_ and cognitive function supports the potential hypothesis of "*PHC → improves cerebral oxygenation → improves postoperative cognition*," as shown in Table 5, researchers have not determined whether the specific mechanism of action is a simple effect of rSO_2_ or a combination of rSO_2_, cerebral oxygen metabolism, brain injury, neuronal apoptosis, and neurotransmitter regulation. In conclusion, both basic studies and large-scale risk factor analyses controlling for other possible confounders of postoperative cognitive function are inadequate, and the specific mechanism of the effect of cerebral oxygen saturation on postoperative cognitive performance is likewise not supported by sufficient evidence.

**Table 5 Tab5:** Summary of studies related to the association between rSO_2_ and postoperative cognitive function

Author	Year	Subjects	N	Oximeter	Outcomes
Trafidlo et al. [81]	2015	Lumbar spondylosis	43	INVOS 5100	NIRS cerebral oximetry may be helpful in reducing postoperative cognitive complications in patients operated on in the prone position
Murniece et al. [82]	2019	Spinal neurosurgery	34	INVOS 4100	The NIRS-based clinical algorithm may help avoid POCD in patients after spinal surgery
Casati et al. [83]	2005	Major abdominal surgery	122	INVOS 4100	A higher rSO_2_ improved MMSE scores in elderly patients undergoing major abdominal surgery

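### The PHC–oxygenation–cognition chain is to be verified from separate between-arm differences, which cannot tell that chain from parallel effects of PHC

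*Protocol article*

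**What the plan says.** At the end of the Background, the protocol adds to its secondary objective on cognition that it will "further verify the existence of the potential mechanism of" PHC improving cerebral oxygenation and so improving postoperative cognition. The Anticipated results section gives the method. Cognitive status on the MMSE in the two groups is combined with the differences between groups in rSO2, Da-jvO2, CERO2, NSE and IL-6, and "a multifaceted and multilevel approach will be used to verify the proposed mechanism of" the chain.

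Other parts of the protocol are more cautious:

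- Anticipated results itself calls the exploration of this possible mechanism a critical objective.
- Statistical analysis labels the secondary results exploratory, with attention to the separate effects of the intervention.
- The Discussion says that "this trial is not originally designed to explore the quantitative relationship between hypercapnia and postoperative cognitive performance". It also leaves open whether any effect runs through rSO2 alone or through several processes.

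The analyses listed under Statistical analysis are t-tests, rank tests, chi-square or Fisher tests, linear regression for the primary outcome, GEE for repeated measures and for the cognitive scale, and ANCOVA for NSE and IL-6. All compare arms or times. The section on venous blood samples mentions an association with cognition for the brain injury markers only, and gives no method.

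**The concern.** A chain has two links: arm to oxygenation, and oxygenation to cognition. Comparing arms on oxygenation tests the first link. Comparing arms on MMSE tests the total effect on cognition, whatever its route. Neither comparison tests the second link, so two favourable arm differences fit a chain and fit two parallel effects equally well.

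Parallel effects are plausible on the protocol's own account. Anticipated results lists free-radical, inflammatory and apoptotic pathways beside oxygenation. Under Study design, setting and participants, the arms also differ in tidal volume and respiratory rate, not only in the PaCO2 target.

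At stake is a secondary mechanistic claim. If both outcomes favour PHC, the text as written invites the statement that the mechanism has been verified, and the data so analysed could not support it. If MMSE does not differ, a real chain may be passed over, because the trial was sized for rSO2. The primary comparison and the sample size are not affected.

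**Working it through.** **1. The plan's own sample size.** Under Sample size calculations, the change in rSO2 is "assumed to be 0% in the control group according to the pilot study". Under PHC a rise of 8 points is taken, one tenth of a starting value of 80%, so the difference between arms is 8 points. The result is that "the total sample size needed for an unpaired t-test was calculated to be 68 at a two-sided significance level of 5% and 90% power". No SD is given, so it has to be back-solved.

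- With SD 10 (assumption), the standardised effect is 8/10 = 0.8. At 34 per arm the noncentrality is 0.8 × √(34/2) = 3.30 on 66 degrees of freedom, and power is 0.9015. The t-test calculation returns 68 in total.
- SD 9 gives 56 and SD 10.1 gives 70, so an SD of about 10 is what reproduces 68.
- 68/0.9 = 75.6, rounded up to 76, or 38 per arm. This agrees with the plan.

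The steps below use 34 to 38 per arm and an rSO2 effect of 0.8 SD.

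**2. Illustrative model.** With X = arm, M = rSO2 change and Y = a cognitive score, all in within-arm SD units:

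- M = 0.8·X + error
- Y = b·M + c·X + error

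Here b is the rSO2–cognition link and c is any effect of PHC on cognition by another route. The documents give neither, so ranges are used. Two ways of reading the data are compared:

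- *Arm-difference reading* (assumed; the protocol states no rule): M and Y both differ between arms in favour of PHC, each at two-sided 5%.
- *Joint reading*: the arm effect on M, and the slope of Y on M adjusted for arm, are both significant and positive.

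Each scenario had 20,000 simulated trials.

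**3. No chain (b = 0).**

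| Other-route effect c | Arm-difference reading confirms | Joint reading confirms |
|---|---|---|
| 0 | about 2% | about 2% |
| 0.3 SD | 21–23% | 2–3% |
| 0.5 SD | 48–54% | 2% |
| 0.8 SD | 82–87% | 2–3% |

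Check at 34 per arm: with b = 0 the two tests are independent, so the first column is the product of their powers. For c = 0.5 that is 0.903 × 0.530 = 0.479, against 0.478 simulated. For c = 0.8 it is 0.906 × 0.901 = 0.816, against 0.817.

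**4. True full chain (c = 0).**

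| Link b | Total effect 0.8·b | Arm-difference reading finds it | Same, any of 3 MMSE visits counts | Joint reading finds it |
|---|---|---|---|---|
| 0.2 | 0.16 | 9–10% | 18–20% | 33–38% |
| 0.3 | 0.24 | 16–18% | 29–32% | 63–70% |
| 0.4 | 0.32 | 24–28% | 40–45% | 84–89% |
| 0.5 | 0.40 | 36–39% | 54–58% | 90–93% |
| 0.6 | 0.48 | 49–54% | 65–69% | 90–93% |

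The three-visit column assumes a residual correlation of 0.6 between visits and used 10,000 simulated trials per scenario.

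**5. Limit of the joint reading.** With no chain and no effect on cognition, but an unmeasured factor loading 0.6 on both rSO2 and cognition, the joint reading falsely confirms in 77–83% of trials. The arm-difference reading does so in about 2%. Randomisation protects the arm comparisons but not the rSO2–cognition slope.

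**The case against.** Several objections have weight.

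- *The protocol contains no pass/fail rule.* This is correct. A reader might infer that the chain will be declared verified whenever both arm differences are significant, but no section says so. The percentages illustrate one natural reading and are not properties of a written procedure.
- *The aim is exploratory.* Anticipated results attaches the critical objective to exploring the mechanism, so it would be wrong to say that verification is called critical. Statistical analysis and the Discussion hedge as well. Even so, the stronger verb stands in both the objective and the description of the method, and the hedges show which wording should give way.
- *The Discussion sentence is not a flat contradiction.* An unpowered secondary look at cognition is compatible with a trial not designed for that question. What does not fit is promising to verify a chain that ends in cognition.
- *A mediation model could sit in an analysis plan that is not shown.* This is fair, and its absence alone is not the point. The point is that the article does state a method, and that method cannot answer the objective.
- *The inputs are undocumented.* The SD is inferred and no value of b or c is given. A reader might conclude that a true chain would usually be missed. That holds for b up to about 0.5 with one cognitive endpoint, or about 0.4 if any visit counts, and fails above. The Background describes the link as contested but does not quantify it. MMSE was also treated as normal, although the section on measuring PNDs notes a capping effect.
- *The alternative is not proof either.* Step 5 confirms this, so it can only be offered as exploratory.

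**Conclusion.** The point holds in a limited form. The stated method, arm differences read side by side, does not answer the stated objective of verifying a causal chain, and the verb conflicts with the exploratory language elsewhere. That follows from the text and needs no simulation.

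The size is illustrative. Under the assumed both-significant reading, with an inferred rSO2 effect of 0.8 SD and 34 to 38 per arm, false confirmation runs from about 2% (no effect on cognition) to 82–87% (another route worth 0.8 SD). The documents do not say where in that range the trial lies, so the top figure should not be quoted alone. A true chain can also be missed, to a degree that depends on an rSO2–cognition link the documents do not give.

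The documents do not support reading this as a flaw in the primary analysis, or as proof that the trial will report a false mechanism. It is a worthwhile and cheap correction to a secondary aim.

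**What to change.** 1. In the Background objective and in Anticipated results, replace verify by explore.
2. Pre-state one exploratory model: postoperative MMSE (or its change) at a named visit, regressed on arm, intraoperative rSO2 change, baseline MMSE and baseline rSO2. Report the indirect effect through rSO2 with its confidence interval.
3. State that the model assumes no unmeasured confounding of rSO2 and cognition, that under strong confounding it too can falsely confirm the chain, and that no confirmatory mechanistic conclusion will be drawn from it.

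The cost is one additional exploratory analysis on data already being collected, and a softer claim. No change to sample size, visits or measurements is needed.

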## Discussion

We will conduct a prospective, single-center, single-blind RCT to assess the effects of interventions on rSO_2_ in patients undergoing laparoscopic colorectal cancer surgery. We will use the absolute change between postoperative and preoperative rSO_2_ values as the primary outcome of the study. Four-time points, T_1_, T_2_, T_3_, and T_4_, are selected to record real-time rSO_2_ and to perform the blood gas analysis and calculations of metabolism-related indicators of cerebral oxygenation. We plan to promptly adjust intraoperative PaCO_2_ and pH on the blood gas results. Notably, the previous clinical focus of hypercapnia has always been on the acidosis and subsequent hyperkalemia that it causes, but one study reported no significant clinical association between hypercapnia and hyperkalemia [77]. In addition, we will dynamically monitor the changes in blood gas parameters at four intraoperative points to ensure trial safety and compliance with ethical guidelines.

On the other hand, the observation of indicators related to cerebral oxygen metabolism and the examination of preoperative and postoperative levels of brain injury markers (NSE and IL-6) provides a further exploration of the comprehensive mechanism of action of PHC to improve the overall cerebral oxygenation function and exert cerebral protective effects. Notably, the majority of previous RCTs on brain protection and postoperative cognition have focused on older adults with good underlying brain function and have used "a history of cerebrovascular accident and/or cognitive dysfunction" as the main exclusion criteria, suggesting that the potential typical beneficiary group of the trial results could not be verified and limiting the externality of the clinical results and contradicting the pragmatic trials currently advocated in the world. Therefore, this study is undoubtedly a potent supplement.

In addition, during the first two hours of the procedure, we will visualize the trend of changes in cerebral oxygenation through the cerebral oxygen monitor to reflect further how the effect of PHC on rSO_2_ changes over time: whether the trend is increasing or decreasing or whether it shows irregular and dynamic fluctuations.

The relationship between PaCO_2_ and CBF has been well documented in recent years, both in terms of underlying physiological mechanisms and in clinical practice, but the relationship between PaCO_2_ and rSO_2_ has not been clarified. Many factors affect rSO_2_, such as cardiac output, volume per beat, MAP, Hb affinity for oxygen, cerebral vascular self-regulation, and surgical position adjustment. Among them, PaCO_2_ may exert a direct and significant effect on the affinity of hemoglobin for oxygen by regulating pH and subsequently through the Bohr effect. Throughout the procedure, we can control for potential confounders such as PaCO_2_, pH, MAP, and intraoperative body position. We will make preoperative baseline adjustments to the subject's MAP, Hb level, and cardiac output. However, intraoperative changes in cardiac output, the brain's self-regulatory effect on the arteriovenous blood volume ratio, the effect of laparoscopic surgery on thoracic pressure, and the subsequent effects on cardiac output, volume per beat and systemic vascular resistance cannot be measured objectively and realistically.

In conclusion, although an increasing number of studies have explored the relationship between PaCO_2_/PHC and rSO_2_ in recent years, the current research evidence only provides an objective description of the clinical phenomenon, as shown in the Table 4. The specific underlying mechanism of action remains unclear, and we should not draw hasty conclusions.

**Table 4 Tab4:** Summary of related studies on the relationship between mild hypercapnia and rSO_2_

**Author**	**Year**	**Subjects**	**Trial**	**Outcomes** (Mild hypercapnia)
Eastwood et al. [78]	2016	Cardiac arrest	Prospective double crossover physiological study	Increases cerebral oxygenation
Akca et al. [79]	2002	Abdominal or orthopaedic surgery	RCT	Improves tissue oxygenation; Increase cerebral oxygen saturation; Reduce the incidence of wound infection
Murphy et al. [27]	2014	Shoulder surgery	RCT	Higher intraoperative rSO_2;_ Lower incidence of CDE
Park et al. [80]	2021	Gynecological Laparoscopic surgery	RCT	Increases rSO_2_
Wong et al. [71]	2020	Elective major surgery	RCT	Associated with a stable increase in rSO_2_

Notably, although theoretical absolute and relative saturation thresholds for the need for rapid intervention have been previously proposed [35], these thresholds have not been validated, and a consensus regarding the indication and timing of interventions is lacking. In our study, we are not yet able to predict the trend and the extent of changes in rSO_2_ in the intervention and control groups, and we will not have intervened in intraoperative rSO_2_ changes if the control group exhibits a slight reduction in rSO_2_ compared to the baseline value and the attending anesthesiologist does not have a clear rSO_2_ target. However, we will consider CDE (≤ 55% absolute change, or a ≥ 20% decrease relative to the baseline) as a marker for administering clinical interventions and stop the intervention when the rSO_2_ increases above the threshold. Although no precise timing for the intervention and a standard intervention has not been established, we will adopt an "*eight-step approach*" for the cerebral oxygen intervention, as shown in the Fig. 3, based on evidence from prior mainstream studies, which has been confirmed to be an effective interventional process in reversing rSO_2_ desaturations [35]. Importantly, for patients with CDE, we will discontinue the trial for emergency unblinding for an intervention, but we will not directly exclude the data from the trial. We will perform an ITT statistical analysis and compare the results with the PP statistical analysis. If the results of both analyses are consistent, the trial will be considered more reliable. In addition, after patients have been randomized into groups, any scenario that might endanger patients' lives and substantially interfere with rSO_2_, such as a massive intraoperative hemorrhage (bleeding of 800 ml or more in a short period or 20% of the total circulating blood volume), severe subcutaneous emphysema, and shock (decompensated period), should promptly result in the discontinuation of the trial, and the ITT statistical analysis will also be needed.

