Among these mechanisms of brain protection, maintaining normal brain oxygenation is one of the most critical factors in ensuring normal brain function. However, as a therapeutic ventilation strategy, any beneficial or detrimental effect of PHC on rSO_2_ in patients undergoing major surgery has not been adequately determined. In previous animal model studies, carbon dioxide was an effective vasodilator, particularly in the cerebral vasculature, with a high sensitivity to improve cerebral blood flow (CBF) [20–22]. The definitive neuroprotective mechanisms of mild hypercapnia are still elusive but are presumably associated with increased CBF, enhanced oxygen delivery, and improved cerebral glucose utilization and oxidative metabolism [23, 24]; moreover, mild hypercapnia may activate adenosine triphosphate-sensitive potassium channels to maintain regular neuronal activity during cerebral ischemic events [13]. Furthermore, in a previous study of PHC applied to the management of clinical anesthesia, PHC increased rSO_2_ and reduced the incidence of cerebral oxygen desaturation events (CDE) in patients undergoing general anesthesia [25–27]. This finding further confirms the existence of potential mechanisms by which PHC directly or indirectly affects cerebral oxygenation.

In recent years, NIRS cerebral oximetry has provided a practical method for the continuous noninvasive measurement of rSO_2_. This method has been used in acute and critical care resuscitation, intensive care, and surgical applications with substantial supporting evidence [28–30]. Many studies have also shown that NIRS can be applied during resuscitation and cardiac surgery to effectively monitor and manage hypoxic events in the brain [31–34]. However, although timely intervention is required when certain absolute and relative brain oxygen saturation thresholds are reached [35], these thresholds have not yet been verified, and agreement on the timing and indications for interventions is lacking. A corresponding increase in rSO_2_ has been reported in patients undergoing major surgery with mild hypercapnia, but the exact temporal relationship between intraoperative rSO_2_ and mild hypercapnia is unclear [9].

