### Randomization and blinding

Random numbers generated by SPSS 25.0 software will be placed in sealed opaque envelopes for patient selection. Patients will be divided into Groups H and N based on random numbers at a 1:1 ratio, and they will not be aware of the grouping. The randomization process will be completed by a study administrator who is not involved in this study. Due to the operational uniqueness of PHC, only patients, data collectors, postoperative followers, and technicians testing blood indicators could be blinded, while clinical interventionists could not. Patients who meet the screening criteria will immediately be randomly assigned to the intervention and control groups. PETCO_2_ will be set accordingly to achieve the desired intervention, but the anesthetist will not have a set rSO_2_ target. Data for all trial outcomes will be collected by an independent researcher unaware of the treatment allocation. After data analysis, the sequences will be decoded. Notably, the anesthetist performing the intervention will not be involved in assessing postoperative cognitive function, and in principle, all study participants should be blinded except for those who are implementing the intervention.

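### Automatic emergency unblinding after a cerebral desaturation event conflicts with the blinding section, tells the ventilating anaesthetist nothing new, and puts blinded outcome assessment at avoidable risk

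*Protocol article*

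**What the plan says.** The protocol article deals with this in two places.

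- **Randomization and blinding.** The division is that "only patients, data collectors, postoperative followers, and technicians testing blood indicators could be blinded, while clinical interventionists could not". The general rule is that "in principle, all study participants should be blinded except for those who are implementing the intervention". On outcomes, "Data for all trial outcomes will be collected by an independent researcher unaware of the treatment allocation", and "the anesthetist performing the intervention will not be involved in assessing postoperative cognitive function". On timing, "After data analysis, the sequences will be decoded". No exception for a CDE is given there.
- **Discussion, on CDE and discontinuation.** "Importantly, for patients with CDE, we will discontinue the trial for emergency unblinding for an intervention", followed by "but we will not directly exclude the data from the trial". These patients go into the intention-to-treat analysis, which is then compared with the per-protocol analysis.

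Three other parts bear on the point. Study design says that real-time rSO2 monitoring is done by investigators who do not give the intervention. Secondary endpoints lists the incidence of CDE as an outcome, together with MMSE on days 1, 3 and 7, delayed neurocognitive recovery (DNR), Ramsay sedation and pulmonary complications. PACU and ward says that ward nurses do not know the grouping.

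**The concern.** The stated purpose of the code break is to allow an intervention. A CDE is an intraoperative event, so it arises while an anaesthetist who set the ventilation by arm is managing the patient. That person already knows the allocation, and opening the code adds nothing to what they can do. Anyone who does learn something from it belongs to a group that the blinding section intends to keep unaware.

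What is at stake is the later, judgement-based assessment. CDE patients remain in the analysis, so their MMSE, sedation and complication records count. DNR rests on a cut-off (a postoperative MMSE of 23 or less together with a fall of more than 2 points), so a single point can decide the classification. The Anticipated results section states a firm expectation that permissive hypercapnia lowers DNR, and that is the setting in which assessor blinding matters most.

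**Working it through.** The main check is a comparison of text. The arithmetic only illustrates direction.

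**1. Who could learn something from a code break?**

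- Anaesthetist ventilating the patient: not blinded, so learns nothing.
- Patient, data collectors, postoperative assessors, laboratory technicians: blinded by name in Randomization and blinding.
- Anyone else not implementing the intervention: blinded in principle by the general rule in the same section. Ward nurses are an example.

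Every person who could gain information is therefore someone the plan means to keep blinded. The Discussion does not say which of them, if any, is told.

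**2. Can both rules be followed for a CDE patient?** One decodes after data analysis with no exception stated. The other opens the code during surgery. For these patients they conflict as written.

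**3. How sensitive is DNR to one point?** Take a baseline MMSE of 26. A postoperative score of 24 is a fall of 2 and is above 23, so not DNR. A score of 23 is a fall of 3 and meets the cut-off, so DNR.

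**4. Would the affected patients be mostly controls?** The protocol gives no CDE rate and no SD, so this rests on assumptions.

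- Inputs from Sample size calculations: mean change 0 (Group N) and 8 points (Group H), two-sided 5%, 90% power, 68 patients (34 per arm), baseline rSO2 60 to 80. The stated final number reproduces: 68 / 0.90 = 75.6, giving 76, or 38 per arm.
- Implied SD by normal approximation: 8 / [(1.960 + 1.282) × √(2/34)] = 10.2. The t-test solution is 10.0. I use 10.
- CDE limit as in Secondary endpoints: a fall of at least 20% from baseline, or rSO2 of 55 or less. The change that triggers it is the larger (less negative) of −0.2 × baseline and 55 − baseline.
- Model: normal change at the end of surgery (T4) only. Share of patients beyond the limit = Φ[(limit − mean) / SD].

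| Baseline | Limit | Group N | Group H | Expected of 38 each | Share in Group N |
|---|---|---|---|---|---|
| 60 | −5 | Φ(−0.5) = 30.9% | Φ(−1.3) = 9.7% | 11.7 vs 3.7 | 76% |
| 65 | −10 | Φ(−1.0) = 15.9% | Φ(−1.8) = 3.6% | 6.0 vs 1.4 | 82% |
| 70 | −14 | Φ(−1.4) = 8.1% | Φ(−2.2) = 1.4% | 3.1 vs 0.5 | 85% |
| 80 | −16 | Φ(−1.6) = 5.5% | Φ(−2.4) = 0.8% | 2.1 vs 0.3 | 87% |

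With an SD of 8 to 12, and a Group H gain of either 8 points or 10% of baseline, the Group N share runs from about 65% to 94%. These are not predicted CDE rates: a CDE can occur at any time in surgery, and the shares hold only if the planned effect is real.

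**The case against.** The strongest reply is that an emergency exception for single patients does not by itself contradict a general rule to decode after analysis. The Discussion does not withdraw the safeguards of the blinding section: the outcome collector is still described as unaware of allocation, and the anaesthetist is still kept out of cognitive assessment. Who is told, and how a break is recorded, is procedural detail that an article may leave to the full protocol.

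Part of this stands. Missing procedural detail is not the point here. But the article states a rule and its purpose, and the purpose cannot be served because the person ventilating the patient already knows the arm. It is also true that the article does not say who carries out the eight-step response and that its flowchart is not shown. Even so, a helper who did not know the arm would fall under the general rule of being blinded.

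Two stronger readings are tempting, and the documents do not support them.

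- *The rule necessarily unblinds the outcome assessors.* The Discussion names no recipient of the code. Patients, technicians and ward staff are blinded too. Assessor unblinding is a risk left open.
- *It happens mainly in control patients.* The Background cites work in which hypercapnia "reduced the incidence of cerebral oxygen desaturation events (CDE) in patients undergoing general anesthesia", and Anticipated results thinks a fall in controls likely. But only one of the five studies in Table 4 lists fewer CDEs, no rate by arm is given, and the Discussion says the trend by arm cannot yet be predicted.

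The reply is also right that the harm is limited. The device-recorded rSO2 endpoint does not depend on an assessor's judgement, and mortality and the ELISA markers hardly do. The Discussion adds that the trial was not designed to quantify the cognitive effect.

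**Conclusion.** The point holds as a conflict between two stated rules. As written, a CDE automatically opens the code for a purpose that the unblinded anaesthetist does not need, and the disclosure can reach only people the plan intends to keep blinded. The consequence is an avoidable risk of assessor bias in MMSE/DNR, sedation and complication ratings for patients who remain in the intention-to-treat analysis. The primary endpoint is little affected.

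The size cannot be fixed from the document. If the planned effect holds, with an SD near 10, about 2 to 12 of 38 controls and fewer than 1 to about 4 of 38 hypercapnia patients would be beyond the CDE limits at the end of surgery, depending on baseline. How many would then be rated by someone who knew the arm depends on who is told, which is not stated. The change is worth making because it is specific and nearly free, not because bias has been shown.

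**What to change.** Reconcile the Discussion with Randomization and blinding:

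- Remove unblinding as an automatic consequence of a CDE.
- State that patients, outcome data collectors, postoperative assessors and laboratory staff stay blinded to allocation after a CDE.
- State that postoperative assessors are not told that a CDE occurred. This should not extend to those who collect rSO2, because CDE incidence is a secondary endpoint taken from the data they record.
- Log any code break that is truly needed, with the time, the reason and who was told.

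The rescue steps and the discontinuation criteria are left as they are. The cost is a few sentences of protocol wording and a simple log, with no effect on sample size or on the analysis.
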